**PROTOCOL SYNOPSIS**

|                                   |                                                                                                                                                                                                                                                                                                                                                                                                                                                                                 |
|-----------------------------------|---------------------------------------------------------------------------------------------------------------------------------------------------------------------------------------------------------------------------------------------------------------------------------------------------------------------------------------------------------------------------------------------------------------------------------------------------------------------------------|
| Protocol Title:            | A Randomized, Intervention, Single-Center Study to Determine the Role of Fatty Acids in Serum and Breast Milk in preventing Retinopathy of Prematurity                                                                                                                                                                                                                                                                                                                          |
| Protocol Number:           | Omega 3-0910                                                                                                                                                                                                                                                                                                                                                                                                                                                                    |
| Number of Subjects:        | 45 subjects receiving Omega-3 supplementation and 45 subjects receiving conventional fatty acid supplementation.                                                                                                                                                                                                                                                                                                                                                                |
| Subject Population:        | 90 premature male/female infants, born before gestational age 28 weeks+ 0 days.                                                                                                                                                                                                                                                                                                                                                                                                 |
| Dosage:                    | All infants on parenteral nutrition from birth and as long as clinically indicated are given fatty acid supplementation (Clinoleic). In addition, children randomized to Omega 3 supplementation receive SMOFlipid® with a quotient between Omega-6 and Omega 3 that is 2.5:1.                                                                                                                                                                                                  |
| Study Duration:            | From birth to 40 postmenstrual weeks                                                                                                                                                                                                                                                                                                                                                                                                                                            |
| Primary Study Objectives:  | 
A) The objective of this study is to determine how fatty acid (FA) levels in prematurely born children are affected by supplementation of “physiologic levels of long chain polyunsaturated fatty acids (LCPUFA) i.e. Omega-3 and 6
 
B) To determine whether these FA levels protect against development of retinopathy of prematurity (ROP)
                                                                                                                       |
| Secondary Study Objective: | 
C) To determine whether these FA levels normalize growth (length, weight, head circumference) and/or
 
D) To determine whether these FA levels reduce the risk of lung, brain and gut morbidity
                                                                                                                                                                                                                                                                     |
| Efficacy Endpoints:        | 
To compare in supplemented versus conventionally treated children
 
A) Serum and breast milk FA levels at days 1, 7, 14, 28 and in postmenstrual weeks 32, 36 and 40 and from breast milk FA levels day 7 and postmenstrual weeks 36 and 40.
 
B) Development of ROP
 
C) SDS score with regard to length, weight and head circumference growth.
 
D) Bronchopulmonary dysplasia, brain development on MRI examination and necrotizing enterocolitis
 |

**Safety Endpoints:** Adverse events, clinical chemistry, retinal exam, physical examination, vital signs.

## List of Abbreviations and terms

|       |                                                              |
|-------|--------------------------------------------------------------|
| AE    | Adverse Event                                                |
| AF    | Amniotic Fluid                                               |
| ALT   | Alanine Aminotransferase                                     |
| AST   | Aspartate Aminotransferase                                   |
| BUN   | Blood Urea Nitrogen                                          |
| CBC   | Complete Blood Count                                         |
| CRF   | Case Report Form                                             |
| CRO   | Contract Research Organization                               |
| ECG   | Electrocardiogram                                            |
| GA    | Gestational Age                                              |
| GCP   | Good Clinical Practice                                       |
| GGT   | Gamma Glutamyl Transferase                                   |
| GMP   | Good Manufacturing Practices                                 |
| GW    | Gestational Week                                             |
| H     | Hour                                                         |
| HC    | Head Circumference                                           |
| ICH   | International Conference on Harmonisation                    |
| IV    | Intravenous                                                  |
| LDH   | Lactate Dehydrogenase                                        |
| Min   | Minute                                                       |
| MPA   | Medical Products Agency of Sweden                            |
| MRI   | Magnetic Resonance Imaging                                   |
| NV    | Neovascularisation                                           |
| QA    | Quality Assurance                                            |
| RBC   | Red Blood Cell                                               |
| REG   | Regionala Etikprövningsnämnden i Göteborg (Ethics Committee) |
| ROP   | Retinopathy of Prematurity                                   |
| SAE   | Serious Adverse Event                                        |
| SD    | Standard Deviation                                           |
| SUSAR | Suspected Unexpected Serious Adverse Event                   |
| US    | Ultrasound                                                   |
| VEGF  | Vascular Endothelial Growth Factor                           |
| WHO   | World Health Organization                                    |

## 1 INTRODUCTION

We hypothesize that when preterm children are deprived of their natural environment they lose important factors normally found *in utero*, such as proteins, essential fatty acids, growth factors and cytokines. Preterm birth is one of the main causes of long term morbidity of different organ systems. It is strongly associated with adverse neurological and cognitive outcome, growth retardation, cardiovascular and pulmonary morbidity, retinopathy of prematurity (ROP) and other ocular and visual disturbances, reflecting exposure to an abnormal environment during the last trimester.

In the eye, normal retinal vascularisation takes place between the fourth gestational month and term. A physiological hypoxia created by increased demands of the maturing retina increases the levels of vascular endothelial growth factor (VEGF) which promotes retinal angiogenesis. In preterm babies, delayed growth of vessels and hyperoxia induced vessel loss may be followed by uncontrolled neovascularisation causing retinal detachment and blindness.

Available treatment with laser and cryo-therapy is based on destruction of the peripheral retina and only reduces blindness by 25%.

In recent animal and human studies we have found that postnatal lack of the growth factor Insulin like growth factor I (IGF1) is associated with ROP and other prematurity related morbidity [1]. In addition, a major binding protein (IGFBP3) protects against oxygen induced vessel loss [2]. These are only two of many substances lost by interruption of placental supply.

The development of the central nervous system (including the retina) which consists of 60% fat is highly dependent on fatty acids for proper development especially during the third trimester when growth is intense. The role of lipids in this process in the regulation of angiogenesis is largely unknown. Human breast milk (HM) contains long chain polyunsaturated fatty acids (LCPUFAs), such as omega 3 (docosahexaenoic acid, DHA) and omega 6 (arachidonic acid, AA), which are the major LCFPUFA components in membranes of the brain and retina, and which are absent from many infant formulas. Breast-fed infants have higher levels of DHA than formula-fed infants and are reported to have better cognitive development [3] and visual acuity, although some studies found no difference between the two groups [4]. In a recent review article it was concluded that preterm infants have a high need for DHA and AA to allow rapid brain and body growth. The content of AA is fairly constant in HM averaging about 0.45% of total FA while DHA levels vary with mothers' diet (0.1-3.8%). A AA to DHA ratio of approximately 1.5 with a DHA content of 0.4% has been recommended for preterm infants[4].

In rats, DHA content in the rod outer segment increases rapidly postnatally from 30 to 70% of total FA [5]. A precursor of DHA is found in the retinal vascular endothelium [6].

In a ROP mice model, we found that increasing the omega-3 PUFA levels by dietary (to the mothers) or genetic means decreased the avascular retinal area by increasing vessel re-growth after injury, thereby reducing the hypoxic stimulus for neovascularisation. Increased levels of omega-3 protected against pathological angiogenesis and the omega-3 derived mediators neuroprotectinD1, resolvinD1 and resolvinE1 also protected against neovascularisation. This protection was to a large part mediated through suppression of tumour necrosis factor  $\alpha$  (TNF $\alpha$ ) which was found in microglia adjacent to retinal vessels [7].

In a double-blind, randomized clinical trial of the effect of omega-3 fatty acids on the oxidative stress of preterm neonates fed through parenteral nutrition has been performed using this dose has been published (8).

The infants recruited in this study is similar to ours, the inclusion criteria were

- (a) gestational age <32 weeks

- (b) birth weight <1500 g
- (c) admission in the ICU within 12 h after birth
- (d) >80% of total energy would be taken in through PN, during the first 8 days of life
- (e) the fat administration through PN would be started on the second day of life at the latest, with the maximum lipid dose being 3 g/kg/day
- (f) anticipated duration of PN would be >7 days.

The source of fat was different for each one of the two groups studied. One group (A) was administered SMOFlipid®, a formulation containing medium-chain triacylglycerols (30%), lipids from soya bean oil (30%), olive oil (25%) and fish oil (15%), while one group (B) was administered the standard lipid formulation with lipids from soya bean oil (Intralipid 20%). Infants in both groups received the PN solutions for a trial period of at least 14 days, at the end of which each infant started oral feedings.

The mean day of life for the onset of enteral nutrition (breast milk) was the same for both groups (group A:  $8.56 \pm 4.67$  days, group B:  $9.46 \pm 5.12$  days,  $P$ -value: 0.702). The volume and rate of administration were similar between the two groups (group A:  $31.78 \pm 17.19$  ml, group B:  $21.03 \pm 12.15$  ml,  $P$ -value: 0.208, group A:  $24.35 \pm 10.49$  ml/kg, group B:  $16.76 \pm 9.52$  ml/kg,  $P$ -value: 0.136). In addition, enteral nutrition was <20% of total daily energy intake for the first 14 days of feeding.

Levels of vitamin E and total antioxidant potential TAP were significantly increased in group A, while in group B only vitamin A levels were significantly increased ( $P$ -value <0.05, data not shown) on the seventh day of the intervention. Body weight was not significantly altered in any group. Blood pressure and heart rate were significantly increased in both groups and at the same rate. Hematocrit values were less in both the groups, again with no difference between them. Hematocrit values were below the normal ranges. Platelet values increased in both groups (within normal ranges), while white blood cell count increased in group A, but still remained within normal ranges. Creatinine decreased significantly in group B (within normal ranges). Regarding vitamin levels, significant differences were observed between the two groups. Vitamin E levels increased only in group A, whereas vitamin A levels increased in both groups. However, there was no significant difference between the two groups regarding vitamin E values, at the end of the fourteenth day. On the other hand, vitamin A values were higher in group A than in group B at the end of the fourteenth day. This could not be completely attributed to the different interventions because there was a significant difference between vitamin A values at the beginning of PN. Moreover, the repeated measures analysis revealed no time  $\times$  group effect for vitamin E and A levels. Interestingly, TAP was increased only in group A and the levels on the fourteenth day were significantly higher in group A than in group B. Moreover, significant time  $\times$  group effect was noticed regarding TAP levels ( $P$ -value=0.001). Hence, the SMOFlipid® dose used for the present study has earlier been shown to be safe and have physiological antioxidant effects.

In addition, safety, tolerability, and efficacy of a novel lipid emulsion containing a mixture of soybean oil, medium-chain triglycerides, olive oil, and fish oil (SMOFlipid 20%) with reduced n-6 fatty acids (FA), increased monounsaturated and n-3 FA, and enriched in vitamin E were evaluated in premature infants compared with a soybean oil-based emulsion (9).

Sixty (30/30) premature neonates (age 3-7 days, gestational age  $\leq 34$  weeks, birth weights 1000-2500 g) received parenteral nutrition (PN) with either SMOFlipid 20% (study group) or a conventional lipid emulsion (Intralipid 20%, control group) for a minimum of 7 up to 14 days. Lipid supply started at  $0.5 \text{ g} \cdot \text{kg body weight}^{-1} \cdot \text{day}^{-1}$  on day 1 and increased stepwise (by  $0.5 \text{ g}$ ) up to  $2 \text{ g} \cdot \text{kg body weight}^{-1} \cdot \text{day}^{-1}$  on days 4 to 14. Safety and efficacy parameters were assessed on days 0, 8, and 15 if PN was continued.

Adverse events, serum triglycerides, vital signs, local tolerance, and clinical laboratory did not show noticeable group differences, confirming the safety of study treatment. At study end,  $\gamma$ -glutamyl transferase was lower in the study versus the control group ( $107.8 \pm 81.7$  vs  $188.8 \pm 176.7$  IU/L,  $P < 0.05$ ). The relative increase in body weight (day 8 vs baseline) was  $5.0\% \pm 6.5\%$  versus  $5.1\% \pm 6.6\%$  (study vs control, not significant). In the study group, an increase in n-3 FA in red blood cell phospholipids and n-3:n-6 FA ratio was observed.

Plasma  $\alpha$ -tocopherol (study vs control) was increased versus baseline on day 8 ( $26.35 \pm 10.03$  vs  $3.67 \pm 8.06$   $\mu\text{mol/L}$ ,  $P < 0.05$ ) and at study termination ( $26.97 \pm 18.32$  vs  $8.73 \pm 11.41$   $\mu\text{mol/L}$ ,  $P < 0.05$ ).

In conclusion, parenteral infusion of SMOFlipid was safe and well tolerated and showed a potential beneficial influence on cholestasis, n-3 FA, and vitamin E status in premature infants requiring PN.

We now want to study whether supplementation of Omega-3 also protects against ROP in humans.

## 2 RATIONALE

### Preterm Child

Most fatty acids, important for development and especially the omega 3 fatty acids for the brain development are transferred in the third trimester with means that in the premature infant this transport via the placenta is interrupted and the infant is dependent on the concentrations in breast milk which vary depending on the mother's diet and her stores. It has even been suggested that low Omega-3 would be a cause of premature delivery (Olsen SF 1992). Many countries have much higher levels of omega3 fatty acids in breast milk than found in Sweden and breast milk substitutions are generally now supplemented with the LCPUFA. Therefore the supplementation to be given cannot be seen to give any risks for the infant. On the contrary, several studies have shown that mother who eat equal to or less than twice fish a week during pregnancy give birth to infants with impaired development (Hibbeln, Landet 2007)

Low Omega-3 levels in premature infants between gestational ages of 23 and 40 weeks can be one reason for ROP development. Restoration of Omega-3 (DHA and EPA) to normal *in utero* levels may prevent ROP by allowing normal vessel growth and survival. An increase of Omega-3 levels bringing levels to within physiological range may prevent development of ROP (7).

### Choice of study drug

Most diets today have high ratio of omega6/omega3 and there are several indicators that the ideal ratio for metabolism (i.e. prostaglandin synthesis) would be a ratio close to 2:1. The conventionally used Clinoleic has a ratio of 9:1, while SMOFlipid® has a ratio of 2.5:1.

### 3 STUDY OBJECTIVES

#### Primary objective

- 1) To determine how fatty acid (FA) levels in premature infants (born with a gestational age below 28 weeks (<28+0)) are affected by supplementation of “physiologic levels of long chain polyunsaturated fatty acids (LCPUFA) i.e. Omega-3 and 6.
- 2) To determine whether these FA levels protect against development of retinopathy of prematurity (ROP).

#### Secondary objective

- 1) To determine whether these FA levels normalize growth (length, weight, head circumference) and/or
- 2) To determine whether these FA levels reduce the risk of lung, brain and gut morbidity

### 4 STUDY DESIGN

The study is a Randomised Intervention, Single-Center Study to Determine the Role of Fatty Acids in Serum and Breast Milk in preventing Retinopathy of Prematurity

Subjects who meet all inclusion and none of the exclusion criteria will be enrolled into the study. Upon entry into the study, subjects will be randomized and given a unique subject number.

A randomised intervention study of 45+45 (number based on power analysis regarding up to date ROP frequency, see 5.1 and 11.1) infants without major malformations born with a gestational age less than 28 weeks + 0 days will be performed.

Randomization of the patients to either

- 1) Conventional fatty acid supplementation regime with Clinoleic (with Vitalipid infant and Soluvit supplementation) to the preterm infant

Or

- 2) SMOFlipid® (with Vitalipid infant and Soluvit supplementation), where the quotient of Omega 6:3 is 2.5:1 in order to mimic the physiologic relation of FAs in cord blood from birth, to the preterm infant.

Thus there is one group of infants (n=45) that will receive Omega-3 in the fatty acid supplementation. The time on parenteral nutrition and the amount of fatty acids given will be according to clinical routines. The randomization of the patients will be performed by the controller of the study Randomization will be in blocks with 10 children in each block.

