### **5.3 Exclusion Criteria**

Subjects presenting with any of the following will be excluded from the study:

1. Detectable clinical gross malformation;
2. Known or suspected chromosomal abnormality, genetic disorder, or syndrome, according to the investigator's opinion;
3. Fish allergy or other severe allergy in the mother
4. Clinically significant neuropathy, nephropathy, retinopathy, or other micro- or macrovascular disease requiring treatment, according to the investigator's opinion;
5. Any other condition or therapy that, in the investigator's opinion, may pose a risk to the subject or interfere with the subject's ability to be compliant with this protocol or interfere with interpretation of results.
6. Bleeding disorder.

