### **6.3 Blinding**

This is a randomised study with blinded ophthalmologic assessment of ROP stage. Retinal examination will be performed approximately once weekly starting at four to five weeks of age according to a standardized protocol and to clinical screening praxis. The assessing, evaluation of ROP stage 3 or more, independent from the study, pediatric ophthalmologists will be unaware which infants are participating in the study.

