#### **10.5 Training**

The Investigator will ensure that appropriate training relevant to the study is given to the medical, nursing and other staff involved. Any information of relevance to the performance of this study is to be forwarded to the co-Investigator and other staff involved.

All investigators signing the protocol and key personnel should provide signed and dated Curriculum Vitae (CV) originals to be filed by the Sponsor. The CV should include name, title, occupation, education, research experience and present and former positions. A staff signature list including delegation responsibilities is required and will be continuously up-dated.

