### **11.1 Determination of Sample Size and Statistical Methods**

#### **Primary endpoint**

The primary endpoint is ROP classified as 0,1,2,3,3+ which is the expected possible range of ROP stages that will be encountered in the study based on analysis of infants screen for ROP in Gothenburg through the years 2004 to 2008. This is an ordinal scale with higher numbers indicating a more severe outcome. The proportion of children with each outcome based on register data is given in table below. In this table an anticipated treatment effect is also indicated by presenting expected outcome in the treated group.

| ROP  | 0 | 1 | 2 | 3 | 3+ | Total |
|-------------|----------|----------|----------|----------|-----------|--------------|
| Control (%) | 26       | 15       | 24       | 18       | 17        | 100          |
| Active (%)  | 49       | 19       | 19       | 9        | 4         | 100          |

Percentage distribution of children with different ROP-outcomes. Control group based on register data and active group based on expected treatment effect.

The estimated treatment effect is based on the following assumptions.

- 25 % of the children will not have any benefit from the treatment.
- 25% will have their ROP reduced one step (e.g. from 2 to 1)
- 50% will have their ROP reduced two steps. (e.g. from 3+ to 2)

The null hypothesis to test is if the distribution ( $F$ ) of ROP ( $X$ ) is the same in both treatment groups.

$$H_0 : F_C(X) = F_A(X)$$

$$H_1 : F_C(X) \neq F_A(X)$$

This hypothesis will be tested with the Mann-Whitney test.

In order to have 80% power at a significance level of 5% a sample of 40 subjects per group is needed (80 subjects in total).

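### A single fixed block size of 10, printed in the protocol of a single-centre trial that states masking only for the eye assessment, lets a well-informed enroller deduce up to one allocation in six

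*Protocol*

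**What the plan says.** The synopsis describes the trial as "A Randomized, Intervention, Single-Center Study to Determine the Role of Fatty Acids in Serum and Breast Milk", with "45 subjects receiving Omega-3 supplementation and 45 subjects receiving conventional fatty acid supplementation". Section 4 gives the allocation method in two statements. The first is "The randomization of the patients will be performed by the controller of the study"; the second is "Randomization will be in blocks with 10 children in each block". No second block size, stratification factor or rule for withholding the block size from enrolling staff is given. Section 4 does place randomisation at entry, after the eligibility criteria have been met.

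The only masking described is in Section 6.3: "This is a randomised study with blinded ophthalmologic assessment of ROP stage". The section goes on to say that the ophthalmologists do not know which infants are in the study. It is silent about ward staff and those who enrol.

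Two other places bear on the point. Section 10.5 asks that "Any information of relevance to the performance of this study is to be forwarded to the co-Investigator and other staff involved" and refers to the investigators signing the protocol. Section 5.3 contains exclusions that rest on judgement, among them "Any other condition or therapy that, in the investigator's opinion, may pose a risk to the subject".

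**The concern.** With fixed blocks, once one arm has used its places in a block, every remaining place belongs to the other arm. Anyone who knows the block size, knows where the block began and can see the earlier allocations can read off the rest. This trial supplies the first item in print. One centre and no stated stratification mean one running sequence, which is the easiest kind to tally.

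The earlier allocations are probably visible too. Section 6.2 describes dosing separately for two named products. Section 9.1 has the investigator record action taken on study medication and judge causality. Section 9.2 requires events related to SMOFlipid to be passed to its manufacturer. These duties make most sense if clinicians know the product, but the protocol never says that they do.

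What is at stake is selection before randomisation. If the next arm is known or likely, the decision to approach a family, or to apply a judgement-based exclusion, can depend on it. The primary test in Section 11.1 is a Mann-Whitney comparison of ROP stage with no adjustment for gestational age, so a prognostic imbalance created at entry would pass into the result. Masked eye examination protects the grading of the outcome; it does not affect who enters.

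**Working it through.** **The plan's own figure.** The protocol gives no predictability figure. Its only design calculation is "In order to have 80% power at a significance level of 5% a sample of 40 subjects per group is needed". Simulating the tie-corrected two-sided test from the two ROP distributions printed in Section 11.1 gives 79.1% power at 40 per group, so that figure reproduces. It is not affected by this point.

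**Inputs.**
- Block size b = 10 (Section 4).
- Allocation 1:1, 45 + 45 (synopsis), so 90 / 10 = 9 blocks.
- Inferred: m = 5 places per arm in each block.
- Inferred: the observer knows all earlier allocations and the block boundaries.

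**Certain allocations.** There are C(10,5) = 252 equally likely balanced blocks. Place k is forced if one arm has used all five of its places among the first k − 1. For k = 6 to 10 this has probability 2 × C(k−1, 5) / 252:

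| Place in block | Calculation | Chance of being forced |
|---|---|---|
| 6th | 2 × 1 / 252 | 0.8% |
| 7th | 2 × 6 / 252 | 4.8% |
| 8th | 2 × 21 / 252 | 16.7% |
| 9th | 2 × 56 / 252 | 44.4% |
| 10th | 2 × 126 / 252 | 100% |

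The sum is (2 + 12 + 42 + 112 + 252) / 252 = 420 / 252 = 1.667 per block. The closed form 2m/(m + 1) = 10/6 agrees. The share is 1.667 / 10 = 16.7%, and over nine blocks 9 × 1.667 = 15 infants of 90.

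**Best-guess rate.** Always guess the arm that is behind, and toss a coin when level. The expected number of correct guesses per block is m + ½ × (2^(2m) / C(2m, m) − 1) = 5 + ½ × (1024/252 − 1) = 6.53 of 10, or 65.3%. Full enumeration of the 252 blocks gives the same.

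**Is 10 too small?** No. For fixed blocks the certain share is 2/(b + 2), so smaller blocks do worse on both measures:

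| Fixed size | Certain | Guess rate |
|---|---|---|
| 4 | 33.3% | 70.8% |
| 6 | 25.0% | 68.3% |
| 8 | 20.0% | 66.6% |
| 10 | 16.7% | 65.3% |

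**Randomly varying sizes.** These figures come from simulation of 90 infants. Sizes are drawn with equal probability, and the observer is assumed to know the set of sizes but not the order in which they occur:

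| Sizes | Certain | Guess rate |
|---|---|---|
| 10 only (protocol) | 16.7% | 65.3% |
| 4, 6, 8 | about 2.3% | about 68% |
| 6, 8, 10 | about 1.6% | about 66% |
| 8, 10, 12 | about 1.3% | about 65% |

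At 1.3%, certain allocations number 0.013 × 90, or about 1 infant, against 15. Varying the size removes nearly all the certainty. The guess rate depends mainly on average block length, so it improves only if blocks become longer and worsens if they become shorter.

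**The case against.** The strongest reply is that the protocol already does much of what is needed. Randomisation belongs to a separate role, the controller of the study. It takes place on entry, after eligibility, and Section 7.3 requires consent before any study procedure. Detailed list handling often sits in a randomisation file that is not shown. All of this stands, so releasing allocations after eligibility need not be asked for again. It does not meet the narrower point, because hiding the list does not stop someone deducing the end of a block of known size from allocations already seen.

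The second reply is that the opportunity is limited. Births before 28 weeks are unscheduled, consent is due within 24 hours with both parents signing (Section 7.3), and lipids start within the first 24 hours (Section 6.2). An infant cannot readily be held back for a later place. This also stands, and it narrows the route to not approaching a family or to using a judgement-based exclusion.

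The third reply is that the premises are inferred. A reader might infer that the protocol declares the trial open-label, or that enrolling staff will in practice foresee one allocation in six. The documents support neither. The protocol does not use the term open-label, does not describe product labelling at the bedside, and has the site pharmacy store and dispense supplies (Section 6.1). One in six requires a complete, ordered tally and known block boundaries. If several people enrol without a shared record, the true figure is lower.

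**Conclusion.** The point holds as a cheap improvement, not as a flaw that undermines the trial. The protocol fixes and prints one block size where the only stated masking is of the outcome assessor. The consequence is at most 15 of 90 allocations known with certainty and a 65% guess rate. This rests on three assumptions: 5:5 blocks, staff who know which product earlier infants received, and a full tally.

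These figures measure predictability, not bias. The documents give no basis for estimating how far the ROP comparison would shift, and nothing in them shows that enrolment was or would be manipulated. Nor do they support a reading that 10 is too small. The weakness is that the size is both constant and disclosed. The sample-size calculation is unaffected.

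**What to change.** Replace the block-size sentence in Section 4 with wording such as: *Infants will be allocated 1:1 in permuted blocks of randomly varying size. The sizes are recorded in a restricted file held by the controller of the study and are not available to staff who enrol or treat infants.*

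Choose sizes that are no smaller on average than now, for example 8, 10 and 12. The often-used 4, 6 and 8 would also cut certain allocations, but would raise the guess rate from 65% to about 68%. The sizes themselves should appear only in the restricted file.

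The cost is a regenerated list and one changed sentence, handled under Section 10.8 if the protocol has already been approved. If recruitment has begun, the new list can start at the next unopened block. The statistical downside is small. Enrolment may end mid-block, and arm sizes could then differ by at most half the largest block (12 / 2 = 6 infants), usually fewer. Under the present scheme, stopping at exactly 80 or 90 gives equal arms.
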